**Figure 1 F1:**
[figure not shown]
**Flow-chart of patient inclusion and data-collection**.

### Definitions

The definitions used in this study were adopted from previous international studies [9-11,13,33-37], Table 1 gives an overview of the used definitions.

**Table 1 T1:** Definitions

An **adverse event **is an unintended injury that results in temporary or permanent disability, death or prolonged hospital stay and that is caused by health care management rather than by the patient's underlying disease process.
A **complication **is an unintended and unwanted event or state during or following medical specialist treatment, that has an unfavourable effect on the health of the patient to such an extend that adjustment of the medical treatment is necessary or that irreparable harm has occurred.

A **near miss **is defined as an act of commission or omission that could have harmed the patient but was prevented from completion through a planned or unplanned recovery.

**Disability **refers to temporary or permanent impairment of physical or mental function attributable to the adverse event (including prolonged or strengthened treatment, prolonged hospital stay, readmission, subsequent hospitalisation, extra outpatient department consultations or death).

**Causation **refers to injury caused by health care management including acts of omission (inactions) i.e. failure to diagnose or treat, and acts of commission (affirmative actions) i.e. incorrect diagnosis or treatment, or poor performance.

**Health Care management **includes the actions of individual hospital staff as well as the broader systems and care processes. Health care management is any care related activity that involves the delivery of care or monitoring of health which is provided by individuals or a team of professionals.

A **preventable adverse event **is an adverse event resulting from an error in management due to failure to follow accepted practice at an individual or system level. Accepted practice was taken to be 'the current level of expected performance for the average practitioner or system that manages the condition in question'.

### Informed Consent and Ethical approval

Eligible patients receive an Informed Consent form with information about the study as soon as possible after admission. Participation in the study is voluntary. Patients are only included in the study after being informed about all the aspects of the study and giving their consent to participate. The signed Informed Consent form will be returned to the researchers to allow further contact during the study. Patients are explicitly informed about the fact that they can terminate their participation in the study at any time without a specific reason and without any negative consequences for future medical treatment. Participants also have the opportunity to consult a physician not involved in the study with questions.

The privacy of the participating patients will be protected; data will be kept separated from patient names. All confidential information will be treated according to the medical confidentiality rules. Each patient will have a specific research code that is not directly traceable to a patient name; these codes are only available to the study researchers. Data related to the study will be stored on a protected server and can only be accessed by authorised members of the research team.

The study protocol is approved by the Medical Ethical Committee of the VU university medical center in Amsterdam.

### Participating surgical wards

Because the researchers will frequently have to visit the participating surgical wards during the study, one hospital region in the Netherlands will be chosen for the recruitment. Although the treatment for hip fractures is fairly standardised by means of protocols, we aim to include a surgical ward of each of the three hospital types that exist in the Netherlands; a university, a tertiary medical teaching and a general hospital. A fourth surgical ward in another hospital will be included as a control group. An inclusion criterion for the surgical wards is that they have to treat at least 100 elderly patients with a hip fracture each year. The wards will be recruited by informing already existing contacts within the wards about the study. If the ward agrees to participate an official intake by the researchers will follow. The nurses in the participating wards will be informed about the study during a meeting. In this meeting the interventions and the inclusion process will be explained. For each ward background information will be gathered about the number of patients, treatment procedures and discharge planning. This will make it possible to compare the wards and correct for important differences.

### Participants

The following inclusion criteria will be used to select eligible patients for participation in the study:

• The patient is acutely admitted to the surgical ward with a hip fracture during the research period;

• The patient is not admitted with polytrauma;

• The hip fracture is not a pathological fracture;

• The patient is 65 years of age or older;

• The patient will be operated on the hip fracture;

• The patient does not participate in an interfering study;

• The patient is in a good cognitive condition to fully understand the information about the study and to give Informed Consent.

Patients will be recruited as quickly as possible after admission to the hospital. The patients will be included by the nurses working in de wards, this process will be closely monitored by the researchers. When a patient is eligible for participation the study will be explained to them and Informed Consent will be asked. If the inclusion by the nurses does not work out as intended, the researchers will have to take over this part of the data collection.

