### Randomisation

In this study surgical wards in three different intervention hospitals and one surgical ward in a control hospital will participate. The eligible patients in the intervention wards will be randomly assigned to one of four intervention groups. Since the SBAR tool cannot be randomised on patient level due to practical reasons, this intervention will concern all patients in the intervention wards. Before the start of the inclusion all Informed Consent Forms and intervention materials will be assigned a unique study number. The study numbers are equally divided over four intervention groups, to ensure equal group sizes as much as possible. All materials for each individual number will be gathered and put into an envelope; the stack of envelopes will be kept in the ward in consecutive order of the study numbers. Each time an eligible patient can be asked to participate, the first envelope of the stack will be used. The process of randomisation is also shown in Figure 2.

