## Discussion

### Strengths and limitations of the study

One of the strengths of this study is the integrated intervention programme that will be implemented in three surgical wards. All three interventions are aimed at improving a different aspect of the care for elderly hip fracture patients. This approach may have more impact than implementing three separate interventions in different situations and could increase the possibility of finding measurable effects in patient outcomes. The randomisation at patient level reduces the influence of the differences between the three wards. In every participating ward the included patients should be equally distributed over the four intervention groups. Another important aspect of this intervention programme is that it focuses on one specific patient group that will increase in the future. The baseline measurement will give insight into the complications and adverse events that affect this patient group. This information will provide valuable insights and possibilities for improving patient safety. Finally, the follow-up of six months enables us to assess the functional recovery of patients and their experiences during those months. These experiences can be used to improve the care after discharge for this patient group and to explore the possibilities for care that is more adapted to their needs.

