### Feasibility

The feasibility of the study depends on a number of factors. First, we are relying on the nurses to include the patients into the trial as they are the first to know when an eligible patient is admitted to the ward. This way, the inclusion can take place as soon as possible after admission. After a few weeks it will become clear whether this method works or not. If the patients are not included by the nurses, the researchers will take over the inclusion process. Second, the success of the intervention programme will depend on the number of available patients, their decision to participate and the loss to follow-up.

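### The group is fixed in an envelope used when the patient is approached, so whoever recruits, nurse or researcher, can know it before consent

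*Protocol article*

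**What the plan says.** All of this is in the protocol article.

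- **Assignment in advance (Randomisation).** "Before the start of the inclusion all Informed Consent Forms and intervention materials will be assigned a unique study number". How the groups are linked to these numbers is described in one sentence, without mention of wards: "The study numbers are equally divided over four intervention groups, to ensure equal group sizes as much as possible".
- **Envelope and order (Randomisation).** Everything belonging to a number goes into one envelope, and "the stack of envelopes will be kept in the ward in consecutive order of the study numbers". The top envelope is taken each time there is an eligible patient to approach.
- **Who recruits (Participants, Feasibility).** The ward nurses do so first. The fallback is stated twice. Under Participants, should recruitment by nurses fall short, "the researchers will have to take over this part of the data collection". Feasibility repeats it: "If the patients are not included by the nurses, the researchers will take over the inclusion process". The second sentence makes clear that inclusion itself passes to the researchers.
- **Eligibility (Participants).** One criterion is a judgement that the patient's cognitive condition is good enough to understand the study and consent.
- **Blinding.** The section covers patients, physicians, both telephone interviewers and the record reviewers. Physicians are said to be unaware of the group because they are not directly involved in inclusion. The recruiter is not mentioned.
- **Ward balance (Strengths and limitations of the study).** "In every participating ward the included patients should be equally distributed over the four intervention groups".

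**The concern.** Randomisation protects a comparison only if the person deciding whether, when and how to approach a patient cannot know the next group. Here the materials that reveal the group come to hand at the approach, before the patient has agreed. A recruiter who sees a card or leaflet in the envelope, or its absence, can present the study differently, wait for another patient, or judge cognition more or less strictly. The patient may also decide with the group in view.

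Intention-to-treat analysis does not repair this. It keeps consenting patients in their allocated group, but patients are included only after consent. Someone who declines after the envelope is opened never enters the analysis, and refusal could differ by group.

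What is at stake is the card and leaflet contrasts. SBAR applies to every patient in the intervention wards, and the control ward is not randomised, so card and leaflet are the only comparisons that patient-level randomisation supports.

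**Working it through.** **Order of events, read from the text**

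1. Study numbers are given to consent forms and intervention materials before inclusion and divided over the four groups. The link from number to group therefore exists before the first patient.
2. All materials for a number share one envelope. Because consent forms carry the same numbers, the natural reading is that the form is inside with the card or leaflet.
3. The next envelope is used at the approach, and consent follows. Anyone who takes the form from the envelope sees the group first.
4. Under the fallback the same steps are carried out by a researcher. No sentence says that this researcher must be someone who did not prepare the list.
5. Steps 1 to 3 apply equally to a nurse. The fallback adds a second possible route, through the list, to a weakness already present in the envelope procedure.

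**Which comparisons are exposed**

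The plan's target is 4 × 80 = 320 randomised patients. Card: groups 2 and 4 against 1 and 3, 160 against 160. Leaflet: groups 3 and 4 against 1 and 2, 160 against 160. No figure in the document allows the selection bias to be sized, since that depends on recruiter behaviour.

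**Secondary check: ward balance**

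Inputs: 320 numbers, 80 per group (Power calculation); three intervention wards (Study design). Assumptions: equal wards, 320 / 3 ≈ 107 patients each, about 107 / 4 ≈ 27 per group; one random order over all 320 numbers. Each case was simulated 10,000 times for one ward, recording the largest minus the smallest group.

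| Division of numbers | Share consenting (assumed) | Mean gap | 95th percentile | Gap of 10 or more |
|---|---|---|---|---|
| Overall only | all | 8.7 | 15 | 39% |
| Overall only | 90% | 8.4 | 15 | 36% |
| Overall only | 70% | 7.8 | 14 | 28% |
| Blocks of 4 in the ward | all | 1.0 | 1 | 0% |
| Blocks of 4 in the ward | 90% | 3.3 | 6 | below 0.1% |
| Blocks of 4 in the ward | 70% | 4.9 | 9 | 2% |

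The 90% and 70% rows apply if an envelope is used up when a patient refuses. Opening it only after consent gives the first row for each method, so the main fix also preserves the balance that blocks provide.

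For the card alone the imbalance is milder. With 107 of 320 numbers drawn and 160 carrying the card, the expected count is 107 × 0.5 = 53.5, with variance 107 × 0.5 × 0.5 × (320 − 107) / (320 − 1) = 17.9 and SD 4.2. One SD either side is 49.3 to 57.7, or about 46% to 54% of the ward. The same holds for the leaflet.

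**The case against.** The strongest reply is that this is a condensed article and its randomisation flow chart is not available here. Sealing, sequence generation, custody of the list and ward-level blocks may all be described elsewhere. That stands, and none of those silences is counted as an error. What remains is the stated order of events: a pre-assigned envelope of group materials, used at the approach. Using the envelope might not mean opening it, and the form might be carried outside, but the text points the other way.

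It can also be said that the fallback is contingent, that the researchers are a team, and that the enroller need not be whoever prepared the list. That is fair. It limits the list route to a possibility and leaves the envelope route untouched.

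A reader might go further and infer from "these codes are only available to the study researchers" that the researchers hold the allocation list and could foresee every assignment. The document does not support this. The sentence belongs to the confidentiality paragraph and concerns a privacy code; nothing equates that code with the study number or with a number-to-group list.

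A reader might also infer that ward differences bias the card and leaflet contrasts, or that the plan contradicts itself on balance. Neither follows. The Discussion states an expectation, the stack kept in each ward may already be balanced, and chance imbalance is noise. The plan also intends to correct for ward and patient differences. Finally, comparisons with baseline or the control ward do not rest on this randomisation, so the consequence is confined to card and leaflet.

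**Conclusion.** The point holds as a weakness in allocation concealment. Under the procedure as described, whoever recruits can know the group before the patient consents, and the fallback comes with no stated barrier between a recruiting researcher and the list. The claim is that foreknowledge is possible, not that any recruiter has it. It rests on two readings: that the consent form is in the same envelope as the intervention materials, and that the envelope is opened when used.

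It affects the card and leaflet contrasts, and the size of any bias cannot be derived from the document.

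Ward balance is secondary. An overall equal division alone would leave an average gap of about 8.7 patients in a ward of about 107, given equal wards and a random order. That costs some precision and weakens the Discussion's argument that ward differences are controlled, but it is not bias.

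**What to change.** - **Randomisation:** keep the numbered consent form outside the allocation envelope. Open the next sealed envelope only after consent is signed.
- **Participants and Feasibility:** state that anyone who recruits, including a researcher who takes over, has no access to the number-to-group list. A team member who does not recruit prepares the list and fills the envelopes.
- **Secondary, Randomisation:** divide the numbers in randomly permuted blocks of varying size within each ward's stack, so that the expected per-ward equality is delivered.

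The cost is a few lines of text and a division of tasks within the existing team. The envelope system and the sample size stay as they are. The downside is that one team member cannot recruit.

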### Randomisation

In this study surgical wards in three different intervention hospitals and one surgical ward in a control hospital will participate. The eligible patients in the intervention wards will be randomly assigned to one of four intervention groups. Since the SBAR tool cannot be randomised on patient level due to practical reasons, this intervention will concern all patients in the intervention wards. Before the start of the inclusion all Informed Consent Forms and intervention materials will be assigned a unique study number. The study numbers are equally divided over four intervention groups, to ensure equal group sizes as much as possible. All materials for each individual number will be gathered and put into an envelope; the stack of envelopes will be kept in the ward in consecutive order of the study numbers. Each time an eligible patient can be asked to participate, the first envelope of the stack will be used. The process of randomisation is also shown in Figure 2.

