### Blinding

In this trial blinding of the patients is not possible as they either do or do not receive the material belonging to the interventions, and are therefore automatically aware of the intervention group. Since the physicians will not be directly involved in the inclusion of patients they are unaware of the intervention group a patients belongs to. For the assessment of the outcomes during a telephone interview two weeks after discharge the interviewer will be aware of the intervention group a patient belongs to because specific additional questions for each intervention group will be asked to evaluate the interventions. However, the interviewer will not be informed about the background, research questions and outcome measures of this study. For the telephone interview six months after discharge the interviewer will be unaware of the intervention group that the patient belongs to. Finally, the reviewers in the retrospective record review study will be blinded, they will assess some of the outcome measures and should therefore be unaware of the interventions that a patient might or might not have received to prevent possible biases in their assessment.

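### As written, the envelope that links a patient to a group is used when the patient is to be asked, not after consent, so allocation concealment is not assured for the card and leaflet comparisons

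*Protocol article*

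**What the plan says.** The Randomisation section of the protocol article sets out four steps.

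- Numbering: "Before the start of the inclusion all Informed Consent Forms and intervention materials will be assigned a unique study number".
- Link to group: "The study numbers are equally divided over four intervention groups, to ensure equal group sizes as much as possible".
- Packing and storage: "All materials for each individual number will be gathered and put into an envelope; the stack of envelopes will be kept in the ward". The stack is ordered by study number.
- Use: "Each time an eligible patient can be asked to participate, the first envelope of the stack will be used".

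The Participants section says who recruits: "The patients will be included by the nurses working in de wards, this process will be closely monitored by the researchers". It has the study explained and consent requested once a patient is found eligible. One eligibility criterion calls for judgement: "The patient is in a good cognitive condition to fully understand the information about the study and to give Informed Consent".

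The Blinding section says of the doctors: "Since the physicians will not be directly involved in the inclusion of patients they are unaware of the intervention group a patients belongs to". It makes no similar statement about the nurses.

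**The concern.** Concealment means that whoever enrols a patient cannot know the coming allocation until the patient is irrevocably in the trial. Here the enrolling nurse handles the envelope at the moment of the approach. If that envelope holds both the form to be signed and the items that define the group, the nurse can learn the group before the patient has decided.

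A nurse who knows that the next envelope holds a card and a leaflet, or nothing extra, may explain the study differently, press more or less for consent, or judge a borderline cognitive state differently. No bad faith is needed. The enrolled groups could then differ for reasons other than chance.

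At stake are the card and leaflet comparisons, which answer research questions 2b and 2c. SBAR applies to every patient in the intervention wards, and the control group is a ward in another hospital, so neither of those comparisons is randomised at patient level.

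**Working it through.** The point concerns the order of steps, so most of the check is reading the sections against one another.

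1. **Does the number fix the group?** Yes. The numbers are divided over the four groups before inclusion starts.
2. **Do the contents reveal the group?** Yes. The four groups correspond to four sets of patient items: neither, card only, leaflet only, both. The Blinding section itself says that receiving or not receiving the items tells patients their group.
3. **Is the consent form in the envelope?** This is inferred. Two sentences before the packing step, the consent forms and the intervention materials are named together as the things that carry a number. The natural meaning of all materials for a number therefore includes the form. The alternative is that only the card and leaflet are packed. That would leave no evident reason to use the envelope when the patient is about to be asked, and the text would still tie its use to that moment.
4. **When is the envelope used?** Combining the sections gives this order: patient found eligible; envelope taken; study explained and consent asked (Participants); pre-fracture questionnaire completed after consent (General data collection and follow up); interventions handed over after inclusion (Strengths and limitations). The envelope comes before consent.
5. **Who handles it?** The ward nurses, since they include the patients. The Blinding section explains the doctors' ignorance of the group by their lack of direct involvement in inclusion. That reason does not cover the nurses.
6. **Does other text restore concealment?** None does. The limitations section lists the randomisation process as a possible influence on outcomes, but discusses only patients in one room exposing each other to the interventions.
7. **Would planned adjustment remove the effect?** Only in part. The Data analysis section provides for correction if patient characteristics differ. The questionnaire covers daily functioning, mobility, nutrition and delirium screening, all relevant to frailty. It is completed only for patients who have consented, and adjustment handles only what it measures.

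**The plan's own figures.** With a difference of 5, a standard deviation of 10, 80% power and alpha 0.05 (two-sided assumed), the normal approximation gives 2 × (1.960 + 0.842)² × (10/5)² = 2 × 7.85 × 4 = 62.8, so 63 per group. The t-test version gives 63.8, so 64, as stated. Four groups of 80 make 320. None of this changes under the concern: all 320 patients pass through the procedure, and weak concealment affects bias, not the sample-size arithmetic.

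**The case against.** The strongest reply is that the text does not establish that nurses see the group. It never states outright that the form is in the envelope, who opens it, or whether the other contents are visible when the form is taken out. Figure 2 charts the randomisation steps and could show a different order, but it is not available here. The route to bias is also narrow: eligibility is settled before an envelope is used, the first envelope must be taken, and the researchers monitor inclusion closely. Choosing whom to approach by group would mean opening envelopes early or departing from the procedure.

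Much of this stands. It lowers confidence, and it makes the way the study is presented the more likely route than the choice of patient. It does not restore concealment, because nothing in the text places the opening after consent.

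A reader might infer more than the document supports:

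- **That patients refuse knowing their group.** The document has patients receive the interventions after inclusion. It does not say that they see the items before consenting.
- **That the sequence is predictable, or the envelopes unsealed.** The article is silent on sequence generation, sealing and opacity. A condensed article may leave these to the full protocol, so silence is not a fault.
- **That every refusal uses up an allocation.** The wording allows this, but the handling of refusals is not described.

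**Conclusion.** The point holds in a limited form. As written, the envelope is used at the approach and, on the natural reading, holds both the consent form and the items that define the group. The nurse can know the group before consent, so concealment is not assured for the card and leaflet comparisons. This is a flaw in the stated order of steps, not a missing detail. It does not show that nurses look, or that the groups will differ.

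The size of any bias cannot be derived from the document. A reader might set an illustrative figure against the 5-point target. Suppose that 30% of eligible patients are frail, with a complication risk of 50% against 25% in the rest. Expected risk is then 0.30 × 0.50 + 0.70 × 0.25 = 32.5%. If half of the frail patients are not enrolled in one group, that group's risk becomes (0.15 × 0.50 + 0.70 × 0.25) / 0.85 = 29.4%, a shift of 3.1 points. If none are lost, the shift is 0. All these inputs are assumptions, the loss of half is severe, and planned adjustment is ignored. The 5-point target is defined for the whole programme, with no separate target for the card or leaflet. The range of 0 to 3.1 points shows only that the answer follows from the assumption chosen.

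Confidence is moderate. The conclusion rests on two things: that all materials includes the consent form, and that Figure 2 does not give a different order.

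**What to change.** Change the order of steps in the Randomisation section:

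- Use one identical consent form for all intervention-ward patients, kept outside the envelope. It should carry no study number until the envelope is opened, because the number is tied to a group.
- Pack only the intervention materials, in sealed opaque envelopes made alike with filler, since the SBAR-only group has no patient items and its envelope would otherwise be recognisable.
- Open the next envelope in sequence only after consent is signed and the pre-fracture questionnaire is complete. Log who opened it and when.
- State that a patient who declines uses no envelope.

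If Figure 2 or the full protocol already gives this order, bring the text into line with it.

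The cost is repacking the envelopes and a short instruction to the nurses, with no added visits or staff. It is easily done before recruitment starts; selection that has already occurred cannot be reliably repaired in the analysis.
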